### Timeline

Development and usability testing of OPEN were completed in November 2012 and RCT recruitment commenced in December 2012. Final follow-up assessment is expected to conclude in January 2014. The study protocol has been approved by the University of British Columbia Clinical Research Ethics Board (certificate number: H12-00493).

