## Introduction

### Background

Arthritis is the most common cause of severe chronic pain and disability [1,2], affecting about 4.6 million Canadians (aged 15 or older) and projected to affect 7 million by 2031 [2]. It is estimated that the majority of these people are affected by osteoarthritis (OA) [3]. Being physically active has been shown to reduce pain, improve quality of life [4-6], and have the potential to slow the progression of joint damage [7]. However, the gap between the *knowledge* about OA management and the *action* of being physically active is extremely large.

Sedentary lifestyle and obesity are predictors of poor health outcomes in people with OA [8-10]. Recent guidelines by the OA Research Society International (OARSI) specifically recommend the use of aerobic, muscle strengthening, and water-based exercises, as well as weight reduction as first line management of knee OA [11], but the majority of people with OA are physically inactive. In 2002, the Arthritis Foundation developed 22 indicators to assess the quality of care in OA [12-14]. When the indicators were applied to a community-based sample in Ontario, 40.1% of people with OA who had no contraindication to exercise had tried exercise [15]. A survey of 1713 people with OA in British Columbia, Canada found that although 79% reported spending time “walking for exercise in the past week”, the majority walked less than one hour per week [16].

Several factors are associated with low participation in physical activities in people with arthritis, some of which are related to the disease (eg, higher levels of pain and fatigue [17-19]), sociodemographics (eg, lower education [20] and income [21]), the person (eg, other commitments, lack of time and motivation [17], doubts about the effectiveness of exercise [19]), and other enabling factors (eg, access to transportation [18], weather [17,18]). People who are newly diagnosed with knee OA tend to have mild pain, stiffness, and functional disability [22]. For these patients, disease-related factors may be a less important barrier to engaging in physical activities. It should be noted that factors associated with physical activity participation were often studied without an overall explanatory framework, making it challenging to develop interventions that work equally well for people with different needs.

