### Randomized Controlled Trial

The efficacy of OPEN is currently being assessed by a proof-of-concept, single-blinded RCT. Individuals with early OA will be identified using validated criteria developed by Marra at al [22]. Eligible participants are those who:

have had pain/discomfort in or around the knee during the previous year lasting over 28 separate or consecutive days,are age 50 years or older,have no previous physician diagnosis of OA, rheumatoid arthritis, psoriatic arthritis, gout, ankylosing spondylitis, polymyalgia rheumatica, connective tissue diseases, or fibromyalgia,have no history of using disease-modifying anti-rheumatic drugs or gout medications,have no prior knee arthroplasty,have not had knee surgery within 4 months prior to enrolling in the study,have no history of acute injury to the knee in the past 6 months,have been physically inactive (defined as participation in moderate intensity activities less than 150 minutes a week) within 6 months prior to study,are not using medication that may impair physical activity tolerance (eg, beta blockers), andhave Internet access and used their email accounts.

People who may be at risk by exercising, as identified by the Physical Activity Readiness Questionnaire (PAR-Q) [43], will be asked to obtain permission from their physicians before enrolling in the study.

Individuals will be mainly recruited from the following sources: (1) community health centers across Metro Vancouver, (2) the ARC website, newsletters, and Facebook site, (3) social networking websites (eg, Craigslist, Kijiji), (4) local television network (community event posting), and (5) local newspapers.

The research coordinator will contact eligible individuals and obtain consent via password-protected email documents. After completing the baseline measures, they will be randomly assigned to the Internet intervention group or the control group in 1:1 allocation ratio. Randomization will be performed using computer-generated random numbers in unequal blocks, which is necessary to ensure adequate allocation concealment.

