The intervention group will receive an emailed password. Participants will receive an automatically generated email prompt to access the website every 2 weeks, with a short newsletter about the ongoing projects at ARC, for the first 3 months. The website will remain accessible throughout the study, but no further prompting emails will be sent after 3 months. In addition, they will receive, by email, an education pamphlet. It will contain information about OA, physical activity, and other treatments.

The control group will receive the same pamphlet by email. For the first 3 months, participants will also receive the same newsletter about the ongoing projects at ARC every 2 weeks by email. During the intervention period, both groups will be able to contact a physical therapist for a consultation via email if they experience increased discomfort after activities.

Outcome measures will be administered online at baseline, 3 months, and 6 months. The primary outcome will be the proportion of participants to meet the American College of Sports Medicine physical activity recommendation of 150 minutes or more of weekly physical activity (moderate or heavy intensity) at 6 months, as measured using the modified Minnesota Leisure Time Physical Activity Questionnaire (MLTPAQ). The MLTPAQ assesses the frequency and amount of time spent on 63 activities in 8 categories: walking, conditioning exercise, water activities, winter activities, sports, garden activities, home repair activities, fishing, and hunting. The average time spent on moderate and heavy physical activity and average weekly energy expenditure (kilocalories/week) will be calculated using the standardized intensity code associated with each activity [44]. It has shown test-retest reliability in both men and women (*r*=.79-.82) [45] and has been validated against caloric intake and treadmill tests [46-48].

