### Sample Size and Data Analysis

Based on the Pharmacist Identification of New, Diagnostically Confirmed OA (PhIND-OA) study [22,37], 40% of residents from British Columbia in Canada (N=194, mean age=62 years) started to exercise after receiving an OA diagnosis and minimal intervention (ie, a pamphlet and the self-management program). We expect that, if OPEN is efficacious, 60% of the intervention group will meet or exceed the recommended level of physical activity at follow-up. Taking into account a 15% loss to attrition over 6 months, 80% power to detect a difference of 20% in physical activity rates between groups and alpha level of .05, a total of 252 participants (126 per group) will be needed. To validate the self-reported physical activity measure, the MLTPAQ, a subsample of 40 participants will be recruited. Assuming we observe a Pearson correlation of .5 for MLTPAQ and VO_2Peak_, a 95% confidence interval around the estimate would range from 0.26 to 0.74.

As the aim of a proof-of-concept study is to demonstrate evidence of efficacy, a per-protocol analysis will be performed. For the primary outcome, dichotomized physical activity participation (ie, yes/no to meeting the American College of Sports Medicine recommendation) from baseline to 3 and 6 months will be analyzed in a logistic regression model after adjusting for the baseline measurement, age, and sex. Intention-to-treat analysis will assess the robustness of the findings. Analysis of covariance (ANCOVA) will analyze the difference in KOOS scores (overall and subscales) between the groups over time. No adjustment will be made for multiple comparisons because Type II error is a greater concern than Type I error in proof-of-concept studies [56,57].

We will examine the mechanisms of OPEN on physical activity participation by conducting mediation analysis using the bootstrapped sampling distribution model by Preacher and Hayes [58,59]. Changes in TPB variables over the intervention period (ie, between baseline and 3 months) will be examined as potential mediators on physical activity behavior at 3 months. In addition, changes in TPB variables over the entire study period (ie, baseline to 6 months) will be examined as potential mediators on physical activity participation at 6 months. Finally, an exploratory analysis using Pearson’s correlations will examine the association between MLTPAQ (ie, energy expenditure) and the VO_2Peak_.

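### Season may confound the 6-month mediation path because enrolment is spread over about eight calendar months; adding enrolment month to those regressions is a free safeguard (low severity)

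*Protocol article*

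**What the plan says.** The Timeline section of the protocol article states that "RCT recruitment commenced in December 2012" and that "Final follow-up assessment is expected to conclude in January 2014". Under Randomized Controlled Trial, "Outcome measures will be administered online at baseline, 3 months, and 6 months", and "Randomization will be performed using computer-generated random numbers in unequal blocks", in a 1:1 ratio.

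Under Sample Size and Data Analysis, the primary outcome "will be analyzed in a logistic regression model after adjusting for the baseline measurement, age, and sex". For mediation, "Changes in TPB variables over the intervention period (ie, between baseline and 3 months") are set against activity at 3 months. For the later time point, "changes in TPB variables over the entire study period (ie, baseline to 6 months) will be examined as potential mediators" of activity at 6 months. The method is a bootstrap of the indirect effect. The article names no covariates for it.

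The Background section lists, among the correlates of low activity in arthritis, "other enabling factors (eg, access to transportation [18], weather [17,18"]). The activity questionnaire includes water, winter and garden categories.

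**The concern.** A mediation analysis has two paths. Randomisation protects the path from treatment to mediator. It does not protect the path from mediator to outcome, where anything that moves both can look like mediation.

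Season is a candidate. OPEN targets perceived opportunity, resources and enjoyment, partly through trails and parks, and good weather could plausibly raise these perceptions as well as activity itself. Participants enter in different months, so they reach the 6-month assessment in different seasons. A change score over exactly half a year carries the seasonal signal at double strength and lines it up with the season of the outcome assessment.

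At stake is one of the named secondary goals, explaining any group difference through the TPB. The Discussion also offers the relation between TPB constructs and activity as what the trial can still deliver if OPEN shows no effect. That relation is the unprotected path.

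**Working it through.** **The plan's own figure.** For 40% versus 60%, two-sided alpha 0.05 (sidedness assumed) and 80% power, the uncorrected size is (1.96·√0.5 + 0.842·√0.48)² / 0.2² = 97 per arm. The continuity correction raises it to 107, and 107/0.85 = 126 per arm, or 252 in total. This matches the protocol and leaves 214 expected completers, 107 per arm.

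**Calendar.** January 2014 minus 6 months is July 2013. Enrolment spans about December 2012 to July 2013, and 6-month assessments about June 2013 to January 2014.

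**Why 6 months is exposed and 3 months is not.** Assume an annual cosine S peaking in mid-July and uniform enrolment over 7.5 months from 1 December.
- At 6 months S has reversed sign, so the seasonal part of the change score is S(6) − S(0) = 2·S(6). With SD of S(6) = 0.729, its covariance with season at the outcome is 2 × 0.729² = 1.06.
- At 3 months, with SDs 0.497 and 0.729 and correlation 0.391, the covariance is 0.497² − 0.391 × 0.729 × 0.497 = 0.106, a tenth as large.
- Over 12 months the seasonal part of the change would cancel.

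**Size of the false path.** Let γ be the seasonal amplitude of the TPB score in SD units, s the seasonal coefficient for activity on the log-odds scale, and V = 0.729² = 0.531. With no true mediator effect, the mediator coefficient is approximately

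b ≈ s · 2γV / (1 + 4γ²V), with SE ≈ 1/√(214 × 0.24 × (1 + 4γ²V)).

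A peak-to-trough swing of 10, 20 or 30 points around 50% gives s = 0.201, 0.405 or 0.619. The last column is P(|Z + b/SE| > 1.96).

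| Swing in activity | γ | b | SE | Path falsely significant |
|---|---|---|---|---|
| 10 points | 0.15 | 0.031 | 0.136 | 6% |
| 10 points | 0.25 | 0.047 | 0.131 | 6% |
| 20 points | 0.15 | 0.062 | 0.136 | 7% |
| 20 points | 0.25 | 0.095 | 0.131 | 11% |
| 30 points | 0.15 | 0.094 | 0.136 | 11% |
| 30 points | 0.25 | 0.145 | 0.131 | 20% |

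Large-sample simulation at γ = 0.25 gives b = 0.046, 0.091 and 0.146 for the three swings, in agreement. Simulation at n = 214 gives path error rates of 6%, 7–12% and 10–19%. Adding season terms brings them back to about 5%.

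**From the path to the planned test.** The plan tests the indirect effect, which also needs OPEN to move the mediator. With OPEN moving it 0.5 SD and n = 214, the indirect effect is falsely significant in about:
- 4–5% of trials at a 10-point swing;
- 7–11% at 20 points;
- 8–17% at 30 points;
- 3–5% once sine and cosine of enrolment month are added;
- 5% at 3 months, with or without those terms.

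In log odds at γ = 0.25, the spurious indirect effect is 0.5 × 0.091 = 0.045 (20 points) or 0.5 × 0.146 = 0.073 (30 points). The planned total effect is ln 2.25 = 0.81, so these are about 6% and 9% of it. At 3 months the value is at most 0.015, even at γ = 0.5.

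**Primary model.** Simulated power without versus with season terms is 83.5% versus 83.7% (10 points), 81.8% versus 83.2% (20) and 84.1% versus 86.7% (30), with Monte Carlo error of about 0.8 point. The SE of the log odds ratio is 0.281 without season and 0.284 to 0.292 with it. Type I error without season at a 30-point swing is 4.3%.

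**The case against.** **Scope.** A condensed article may leave mediation covariates to the full protocol or analysis plan, so their absence is not an error. That stands. What remains is that the article itself fixes the mediator window and the outcome time, and this pairing creates the exposure. The point is therefore offered as an improvement.

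**No seasonal size is documented.** This stands too. Weather is listed only as a correlate of activity, and nothing says that season moves TPB scores. A 30-point swing exceeds the 20-point treatment effect the trial is sized for. The questionnaire also counts winter activities and conditioning exercise, so people may switch activities and flatten the swing. Only *may be confounded* is supported.

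**The indirect effect is harder to mistake than the path.** With season shifting mediator and outcome by 0.4 to 0.5 SD, a false indirect effect appears in about 0.2–0.3% of trials if OPEN does not move the mediator, 3–6% if it moves it 0.3 SD, and 7–11% at 0.5 SD. The inflation therefore depends on OPEN working on the mediator.

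**Stronger readings to resist.** A reader might infer that the half-year gap alone causes the problem. It does not: the gap is common to both arms and to any 6-month follow-up, and if everyone enrolled in one month season would be constant. A reader might infer that the primary comparison is biased or loses precision. It is randomised, and both arms are assessed on the same schedule. Omitting a prognostic term from a logistic model pulls the odds ratio towards 1 and lowers its standard error, so the cost is a little power. A reader might also worry about within-arm change after the email prompts stop, but the article plans no such analysis.

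**Conclusion.** The point holds as a low-severity, cost-free improvement to one secondary analysis. The mediator-to-outcome path at 6 months may be confounded by season. Under assumed swings of 20 to 30 points in activity, a seasonal amplitude of 0.15 to 0.25 SD in TPB scores and a 0.5 SD effect of OPEN on the mediator, the false-positive rate of the indirect effect is about 7% to 17% instead of 5%. At a 10-point swing there is no clear excess. The 3-month mediation model is essentially unaffected. The primary contrast is valid as specified, and no stated figure is wrong.

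**What to change.** Add sin(2π × month/12) and cos(2π × month/12), with month taken from the randomisation date, to both regressions of the 6-month mediation analysis (mediator on treatment, and outcome on mediator and treatment). Using the randomisation date keeps the terms fixed before any treatment effect. Because the assessment falls six months later, they also describe season at the outcome.

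The same two terms may be added to the primary logistic model for about 1 to 3 points of power at swings of 20 to 30 points. That is optional, and if done it should be specified before outcome data are examined.

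The cost is two model terms built from dates the trial already holds, and one sentence in the analysis section.

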## Discussion

The proposed study will be one of the first to evaluate a theory-informed behavioral intervention at a time when people tend to be more motivated to adopt an active lifestyle (ie, at the “teachable moment”). Our approach, consisting of identifying people with early knee OA using a set of validated criteria [22] followed immediately by an online intervention that directly targets physical inactivity, can be easily implemented across communities. This proof-of-concept study will provide a foundation to further study and implement lifestyle interventions in managing chronic musculoskeletal conditions. If the intervention is found to be effective in changing physical activity behaviors, it will open further opportunities to promote early diagnosis and to implement lifestyle interventions. Conversely, if the intervention shows no difference in improving physical activity behavior compared to the control, this study will still offer the opportunity to examine relationships between the TPB constructs and physical activity participation.

The OPEN project also has potential to improve primary and community-based care in people with arthritis. The value of this project is summed up by our Knowledge User Co-Investigator and a primary care physician, [name]:

I see the impact of physical inactivity on my patients daily. Even though I work within an interdisciplinary team environment specifically designed to manage chronic disease, we still struggle to consistently motivate and educate our patients about how to increase their physical activity…I see the innovative approach of OPEN as an excellent initiative to educate patients about osteoarthritis, but more importantly customize and realize their physical activity goals. Simply, we need this type of tool in our clinical practice.

The partnership with Centre for Digital Media allows for the development of OPEN using the latest digital media technologies and provides training to digital media students in health research. Once the research is completed, OPEN will be available free of charge for public use.

## Abbreviations

ANCOVA: analysis of covariance
ARC: Arthritis Research Centre of Canada
BMI: body mass index
KOOS: Knee Injury & Osteoarthritis Outcome Score
MLTPAQ: Minnesota Leisure Time Physical Activity Questionnaire
OA: osteoarthritis
OARSI: Osteoarthritis Research Society International
OPEN: Osteoarthritis Physical Activity and Exercise Net
PAR-Q: Physical Activity Readiness Questionnaire
PBC: perceived behavioral control
PhIND Study: Pharmacist Identification of New, Diagnostically Confirmed OA Study
RCT: randomized controlled trial
TPB: Theory of Planned Behavior
VO_2Peak_: maximum aerobic capacity
WOMAC: Western Ontario MacMaster OA Index
